**Satisfaction with the park**	
I am satisfied with:	
The quality of the park	1) strongly disagree, 2) disagree, 3) neither agree or disagree, 4) agree, 5) strongly agree 6) don’t know
The facilities available	As above
The playground	As above
The walking/cycling tracks	As above
The maintenance of the grounds and facilities	As above
The dog walking facilities	As above
**Health-related measures**	
In general, would you say your health is	1) excellent, 2) very good, 3) good, 4) fair, 5) poor
**Child variables***	
Age	Years
Sex	Male/Female
Are they with you in the park today?	Yes/No
Have they ever visited this park?	Yes/No
In the past 3 months, on average, how often have they visited this park?	1) daily, 2) 2–3 times per week, 3) once per week, 4) 2–3 times per month, 5) once per month, 6) < once per month, 7) first time to this park
What do they usually do when at this park?	Open ended
Who do they usually come with to this park?	1) alone, 2) adult, 3) friends, 4) organised group, 5) dog, 6) other

*Proxy-reported by adult for child aged 2–15 years who has the next birthday.

At T1, trained, clearly identifiable research assistants approached park users in the specified target areas, explained the study and all ethical considerations, and invited participation. Participants were also asked if they had a child(ren) aged 2–15 years, and if so, they were asked to consider the child in the age range who had the next birthday and answer additional questions relating to this child’s use of the park. Overall, 794 park users agreed to participate (75.3% of those approached, excluding those who had already completed an interview). A total of 313 interviews were conducted at the intervention park (73.6% of those approached) and 481 interviews at the control park (76.5% of those approached). The child questions were completed by 366 (46.1%) participants overall. The main reasons for non-participation apart from already having completed the survey (44%) included: too busy/no time (21%), did not want to stop exercising (8%), were not interested (6%) and/or did not speak English (4%).

### Electronic path monitors and car traffic counters

Electronic path monitors were used at T1, and will be repeated at T2 and T3 to record the number of people walking and cycling on two pre-selected paths at both parks. The monitors incorporate the use of an infra-red beam and counter and are positioned at a height to include counts of children but to exclude counts of dogs (very large dogs may have been counted). At T1, two path monitors were positioned at the same location over the eight days of data collection at both parks. The path monitor location was decided by Parks Victoria rangers at each park, along with research staff. The locations were areas that were used most frequently and were most comparable between the two parks. Both parks incorporate a path that enables transport to the Melbourne CBD and one monitor in each park was positioned to record this traffic. The path monitors were set up at 7:30 am on weekdays and 8:30 am on the weekend days and were removed at 4:30 pm.

At T1 a traffic counter was located on the road at the entrance to both parks to record the number of vehicles entering and exiting the parks (hourly counts) over the 14-day period that incorporated the days when park observations were conducted. This will be repeated at T2 and T3.

## Discussion

The refurbishment of this large suburban park in a low SES area affords a unique opportunity to evaluate a ‘real world’ natural experiment. There is increasing interest in using the opportunities presented by natural experiments to generate evidence about population health impacts [47]. This study provides novel evidence for policy- and decision-makers regarding the role of parks for increasing community physical activity levels. Moreover, the location of the intervention park in a disadvantaged area will help inform the extent to which interventions of this type can beneficially influence the physical activity of those at higher risk in the population. Strengths of the study design include the wide range of comprehensive measures and the inclusion of partners which was integral to the data collection and will greatly assist the dissemination of results to key stakeholders. Previous research has suggested that building meaningful partnerships with diverse communities can improve health outcomes [48].

However, many challenges must be overcome in the development and implementation of this type of intervention study. One challenge of natural experiment research is timing the completion of measures with an unpredictable and frequently changing intervention timetable which is completely outside the researchers’ control [26]. The refurbishment works at Brimbank Park were delayed on numerous occasions, and significant negotiation and flexibility was required to co-ordinate the research funding availability with the intervention schedule. Typically, once grant money is awarded, data collection cannot be delayed indefinitely to accommodate delays in building works. Flexibility is therefore required by funding bodies to accommodate events outside of the researchers’ control.

An additional challenge is the ability to identify equally matched intervention and control parks. In the current study, it was not possible to match the parks according to area-level SES, hence the control park is located in a high SES neighbourhood and intervention park in a low SES area. However, given that the objective was to compare differences in changes in park use and in park-based physical activity between the intervention and control park, the study design will overcome this mismatch for area-level SES.

An additional uncontrollable factor was the constraint of weather. Although at T1 observation days with forecast rain were rescheduled (which required flexibility within the field team), weather conditions that were not severe enough to postpone data collection, such as light drizzle, very cold mornings and windy days, may have affected park usage. Although the unpredictable weather was a limiting factor, the forecast and actual weather conditions for each observation day were recorded and will be used when interpreting the results. Further, despite regular communication with park rangers, events often occurred in the park without our prior knowledge (i.e. burning areas of overgrowth for fire control, school excursions and community events) and such events may have resulted in atypical numbers of park-users. In addition, the large size of the intervention park meant that observers were unable to observe all park areas and observations were only conducted in the specified target to areas; however, the use of electronic monitors to record path usage and traffic will assist with monitoring of usage of the park outside the targeted observation areas.

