**Methods:**

The intervention park is a large regional park (329 hectares) located in a low socio-economic status (SES) area in the north-eastern suburbs of Melbourne, Australia. The control park is a regional park (120 hectares) located in a high SES area in the eastern suburbs of Melbourne. Multiple methodologies to evaluate the impact of the park renovation are being employed including: cross-sectional surveys of local residents living near the two parks, direct observations of park users, intercept surveys with park users, and electronic monitoring of path usage and car traffic within the parks. Baseline measures were conducted in April-May 2013 (T1), and an innovative play space suitable for children of all ages and abilities was installed at the intervention park between September 2013 and February 2014. Follow-up measures will be repeated in April-May 2014 (T2) and April-May 2015 (T3). All methodologies will be completed at both the intervention and control parks at all three time-points, with the exception of the cross-sectional survey of local residents which will only be conducted at T1 and T3.

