#### The control park

Westerfolds Park (120 hectares) is located 22 km east of Melbourne’s CBD. This park was selected to match as closely as possible to the intervention park prior to refurbishment using the following criteria: 1) park features (i.e. mainly open spaces and picnic areas); 2) park size; 3) accessibility via a shared walking/cycling path; and 4) availability of a sealed walking/cycling path within the park. The control park is located in a more socio-economically advantaged area of Melbourne; however, it was not possible to find a matching large park in a disadvantaged area with similar features to the intervention park. Importantly, there are no planned improvements or changes to the control park during the study period.

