## Methods

Baseline data collection occurred in April-May 2013 (T1, prior to the refurbishment commencing), in both the intervention and control parks. Follow-up will be conducted at both parks at one-year intervals, Time 2 (T2, 2014) and Time 3 (T3, 2015) with each data collection to take place at the same time of the year to account for seasonal effects. The inclusion of two measures post-refurbishment allows time for residents to become aware of the new facilities [32]. To address the study aims, multiple methodologies will be employed including: cross-sectional surveys of local residents living nearby the two parks, direct observations of park users, intercept surveys with park users, and electronic monitoring of path usage within the parks and of vehicles entering and exiting on-site car parks.

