#### Survey

The 91 item self-report survey was designed to include measures of the outcome variables (park usage, physical activity and active travel), potential determinants of these outcomes and relevant covariates. Respondents with a child(ren) aged 2–15 years living in the household, were asked to consider the child in the age range who had the next birthday and complete additional proxy-report survey questions regarding that child’s use of parks and related behaviours.

A socio-ecological framework [34] was used to develop the survey instrument which measured all three levels of influence on behaviours (intrapersonal, social and neighbourhood environmental influences). The survey included socio-demographic variables (age, sex, country of birth, marital status, employment status, highest level of education, motor vehicle access, dog ownership, time spent living at residential address and in the neighbourhood, and number of children) and participants self-reported their weight and height.

Where possible, established survey items from the literature with known reliability and validity were used. Self-reported transportation and leisure-time physical activity and time spent sitting in the last seven days was examined using the long form of the International physical activity questionnaire (IPAQ-L) [35]. Four items examined self-reported stress [36], ten items examined self-reported depression. CES-D10 [37] and a single item examined self-reported general health using the Short Form Health Survey (SF-36) (http://www.rand.org/health/surveys_tools/mos/mos_core_36item.html).

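### Comparing changes removes only fixed SES differences; with one baseline wave and one park per arm, the Discussion cannot claim that the SES mismatch is overcome

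*Protocol article*

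**What the plan says.** All references are to the Protocol article.

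- The abstract (Methods) describes one park per arm: "The intervention park is a large regional park (329 hectares) located in a low socio-economic status (SES) area" and "The control park is a regional park (120 hectares) located in a high SES area in the eastern suburbs of Melbourne".
- The section on the control park admits the imbalance, "The control park is located in a more socio-economically advantaged area of Melbourne", explains that no comparable large park in a disadvantaged area could be found, and adds that no works are planned at the control park during the study.
- The Methods section gives one wave before the works: "Baseline data collection occurred in April-May 2013 (T1, prior to the refurbishment commencing". T2 (2014) and T3 (2015) both follow completion in February 2014. The neighbourhood survey is a repeated cross-section at T1 and T3 only.
- The Discussion repeats that "the control park is located in a high SES neighbourhood and intervention park in a low SES area". It reasons that "the objective was to compare differences in changes in park use and in park-based physical activity between the intervention and control park" and concludes that "the study design will overcome this mismatch for area-level SES".

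The article states no parallel-trends assumption and names no residual limitation from the SES mismatch.

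**The concern.** The Discussion discloses the main confounder and then declares it dealt with. Comparing changes deals with a mismatch in level. It does not deal with a mismatch in how park use or activity was already moving, or would have moved without the play space. Areas at opposite ends of the SES range could plausibly differ in that respect over two years.

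At stake is what the trial can conclude. The article offers the results to policy-makers as evidence on parks in disadvantaged areas. A differential background trend would be read as an effect of the play space or, if it ran the other way, would hide one. A reader who takes the sentence at face value would not look for either.

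**Working it through.** **1. What a difference in changes estimates.** No figure in the article underlies the claim, so the first check is design logic.

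Difference in changes = effect + (background trend in intervention area − background trend in control area).

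Constant differences between the areas drop out. The bracket does not.

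**2. Whether the design can examine the bracket.**

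- Pre-intervention trend contrasts = pre-intervention waves − 1 = 1 − 1 = 0. T2 and T3 are both post-refurbishment and add none.
- Survey: 2 parks × 2 waves = 4 cells. Intercept, park, wave and park-by-wave use 4 parameters. The effect and a differential trend are the same fourth term.
- Three-wave measures (observation, path monitors, traffic): 2 × 3 = 6 cells, with 1 + 1 + 2 + 2 = 6 parameters. Nothing is left to estimate how far change varies between parks.

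**3. Who responds.** Baseline response was 15.4% (schools) and 15.5% (Councils). A change in respondent mix that is the same in both areas cancels. One that differs between areas and is related to the outcome does not.

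**4. Illustration of size.** The documents give no differential trend, so the trend sizes are assumed. The true effect is set to nil.

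*(a) At the baseline number of respondents.* Assumptions:

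- 1,488 respondents at each wave. The article reports this for T1; it is assumed for T3.
- An equal split between areas, 744 each, which the article does not report.
- Independent respondents and no covariates.
- A factor 1 − Σp³ = 0.898 in Whitehead's ordinal formula. This is not in the article. It is back-solved by reading 444 as a per-group size: 6(1.96 + 0.84)²/(ln 1.41)² = 399, and 399/444 = 0.898. The article says 444 at each time point and gives no category distribution, so that reading is neither confirmed nor refuted.

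Variance of the log OR at one wave = 6/(744 × 0.898). The change comparison doubles it:

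SE = √(24/(1488 × 0.898)) = 0.134.

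False-positive rate = P(|Z + ln(t)/0.134| > 1.96), where t is the differential trend as a ratio of ORs.

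*(b) At the planned sample size.* The SE is taken from the planning parameters (OR 1.41, two-sided 5%, 80% power), so 0.898 is not needed: ln 1.41/(1.96 + 0.84) = 0.123 for a post-only comparison. Multiplying by √2 gives 0.173 for a comparison of changes with the same cell sizes.

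| Assumed differential trend (OR) | (a) SE 0.134 | (b) SE 0.173 |
|---|---|---|
| 1.1 | 11% | 9% |
| 1.2 | 27% | 18% |
| 1.3 | 50% | 33% |

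Varying the factor in (a) from 0.75 to 0.98 gives 10-12%, 24-30% and 43-53%. All three assumed trends are smaller than the planning OR of 1.41. The bias itself does not depend on sample size; a larger sample only makes it more likely to reach significance.

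**The case against.** The case for the article is partly sound. It discloses the SES mismatch openly and explains that no better control park existed. Comparing changes does remove fixed SES differences, which is the narrow reading of the sentence. Measurement in the same season and the absence of planned works at the control park remove some other sources of differential change. The single baseline wave and the single control park cannot now be altered. All of this stands. It shows that the design reduces the problem, not that it overcomes it: excluding planned works says nothing about area-level trends.

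Some stronger readings are tempting, and the documents do not support them.

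- *Park size.* The parks differ in area (329 against 120 hectares) although size was a matching criterion. Area is fixed over the study, so any constant effect of it cancels. It adds nothing to an argument about trends.
- *Low response.* Response of about 15% is a baseline level. It is not evidence that the respondent mix will change differently in the two areas.
- *The false-positive rates as a forecast.* No differential trend is documented, and the percentages depend on every assumption listed with them.
- *Misleading confidence intervals.* The article does not specify the survey model, so one cannot say that its intervals will ignore this error. The illustration shows only what a simple analysis of independent respondents would do.
- *Covariates as a cure.* The survey collected individual SES measures ("The survey included socio-demographic variables (age, sex, country of birth, marital status, employment status, highest level of education", among others). Adjusting for them cannot remove area-level trends that are aliased with the intervention, and the described observation, path-monitor and traffic data carry no SES variables.

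**Conclusion.** The sentence in the Discussion is wrong as written. The conclusion rests on the form of the estimate and on the counts of one baseline wave and one park per arm, all stated in the article; it does not rest on the illustrative percentages. Differential SES-related trends, and differential outcome-related shifts in who responds, remain in the estimate and cannot be tested or separated from the play space.

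How much this matters in practice is unknown, because the size of any differential trend is unknown. The illustration shows that trends well below the planning effect could matter. This does not make the comparison worthless or show that it is biased. The design lacks a property that the article claims for it, and the claim should be corrected.

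**What to change.** 1. Replace the sentence in the Discussion with wording such as: *Comparing changes removes time-constant differences only. It assumes parallel trends, which one baseline wave and one park per arm cannot test, so differential SES-related trends remain a limitation.* Limit causal conclusions accordingly.
2. In the survey models, include the SES variables already collected (education, employment, country of birth, vehicle access) and their interactions with wave. Describe this as partial adjustment for trends and compositional shifts that act through measured individual SES. State that it does not remove area-level trends and cannot be applied to the SOPARC, path-monitor or traffic counts.
3. For each main outcome, report how large a differential trend would explain away the estimated effect.

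The cost is a text change, extra model terms on data already collected, slightly wider intervals and a more modest claim. No new data collection is needed.

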## Conclusions

Despite these challenges, REVAMP will provide valuable unique insights into the impact of park refurbishment on park use and park-based physical activity and the development of natural experiment methodology. The findings will also provide information for future park developments and refurbishments and have the potential to assist urban planners and park designers to develop parks that are relevant to the communities they serve, attract users and encourage park users to be physically active.
